### **Safety evaluation**

All subjects who received one trial drug will be eligible for safety analysis. Subjects' physical examination results, vital signs, adverse events, and laboratory outliers were summarized. Subjects must be closely monitored for adverse events. The severity of adverse events was graded according to CTCAE (V5.0) standard, and the severity, severity and relationship with the experimental drug should be evaluated.

The investigator was responsible for evaluating the association of all adverse events with the investigational drug. However, the principal investigator may authorize the judgment of other qualified clinicians participating in the study, but is still responsible. The investigator must provide a list of qualified and authorized personnel.

### **Adverse events**

#### **Definition of adverse events**

Adverse events refer to all adverse medical events that occur after a subject receives an investigational drug, can show the signs and symptoms of disease or laboratory abnormalities, but does not necessarily have causality with experiment with drugs. In the clinical study, adverse events can happen is to accept test after using drugs, any time bad health condition.

Examples of AE include:

- 1) Exacerbation of pre-existing chronic or intermittent diseases, including increased frequency and/or intensity;
- 2) New diseases discovered or diagnosed after the trial drug was administered, even though they may have existed before the study began;
- 3) Physical signs, symptoms or clinical sequelae of suspected interactions;
- 4) Experimental drugs or combinations of drugs, suspicious signs, symptoms, or clinical sequelae due to drug overdose;
- 5) Signs and symptoms that are time-dependent with treatment;

### **Unexpected adverse events**

An unintended adverse event is any adverse drug event whose character or severity is inconsistent with the investigator's manual (or the control drug label). The addition of significant information about the nature or severity of known or documented adverse events is also part of the reporting of unintended adverse events. For example, events that are more special or severe than those described in the researcher's manual should be considered "unexpected".

### **Observation, recording and reporting of adverse events**

All adverse events that occurred after the subject received the investigational drug, which will need to be fully documented on the subject's case report form or eCRF.

Description of each adverse event should include its start and end date, whether it conforms to a serious adverse event, measures taken (such as study treatment changes, other treatments and follow-up tests) and outcome, and request the investigator to conduct a causal evaluation (relationship to study treatment). Adverse events should be graded and changes recorded on the corresponding case report form or eCRF. Documentation must be supported by original data.

### **Methods for detecting adverse events**

At each follow-up, adverse events can be detected by:

Unsolicited information provided by the subject or caregiver

At each visit, subjects were asked open-ended, non-leading questions: How are you feeling? Have you had any medical problems since your last visit?

Abnormalities observed by the investigator, other medical staff, and family members.

Abnormalities detected by medical tests and examinations

Other Abnormal conditions

### Adverse event collection time

Adverse events were recorded from the time subjects received the investigational drug to 21 days after the drug was administered.

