**Table 1: Dose escalation protocol for single dose trials in healthy subjects**

| array | Dose (mg) | Number of healthy subjects (n)    |                                     |
|-------|-----------|-----------------------------------|-------------------------------------|
|       |           | Experimental group                | Control group                       |
|       |           | long-acting ropivacaine injection | ropivacaine hydrochloride injection |
| A     | 150       | 6                                 | 3                                   |
| B     | 230       | 8                                 | --                                  |
| C     | 300       | 8                                 | --                                  |
| D     | 350       | 8                                 | --                                  |
| E     | 400       | 8                                 | --                                  |
| Total |           | 38                                | 3                                   |

Positive control was set for cohort A, and no positive control was set for other dose groups. The study began at the minimum dose, with each subject receiving only one dose and only one dose cohort at a time. Safety assessments were conducted on days 7 and 21 after dosing, and the next cohort/batch trial was determined based on the results. If no significant adverse effects were observed in the maximum dose cohort (400mg), dose-escalation was not continued.

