### **Adverse events**

Any subject receiving the investigational drug should be assessed for safety. The evaluation period shall be from the time of receiving the investigational drug to 21 days after the end of study or administration. AEs or SAEs occurring during this period shall be followed until they return to normal or stable (except for subjects who are dead, lost to follow-up, or have withdrawn their informed consent).

Adverse events were coded using MedDRA.

In this study, the adverse events (TEAE) occurred during treatment were mainly analyzed statistically. The adverse events occurred during the screening period to before the first administration were listed, but the statistical analysis of adverse events was not included.

Adverse events referred to below refer to adverse events occurring during treatment.

The incidence, number and incidence of all adverse events, drug related adverse events, serious adverse events and abortion related adverse events in each group were calculated.

According to systematic organ classification (SOC) and preferred term (PT) classification, the number of adverse events, the number of cases and the incidence of adverse events in the two groups were calculated.

A list of adverse events related to the study drug during treatment, a list of all adverse events, a list of adverse events resulting in shedding, and a list of serious adverse events were listed separately.

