- 17) After screening, subjects should be asked whether they suffer from acute diseases; Have you taken any alcohol-based products in the 24 hours prior to study administration; Whether you exercise vigorously; Whether to maintain a good living condition; Drink (or consume) theophylline, caffeine, theobromine, and alcohols 48 hours before administration of the study drug.
- 18) Determination of analgesic range: 15min, 30min, 45min $\pm$ 3min, 1h, 1.5h, 2h, 3h, 4h, 5h, 6h, 7h, 8h, 9h, 10h, 11h, 12h  $\pm$ 5min after the single point of administration, pain points were determined in two directions (when the VAS value of the test point (n) 1cm away from the point of administration was  $\geq 4$ , The measurement can be terminated at (n+1) time point), the distance between pain point and drug administration point (R1, R2), analgesic range diameter D = (R1 + R2) were measured and recorded.
- 19) Local skin irritation at the injection site: within 30min before injection, 20min, 40min $\pm$ 5min, 1h, 2h, 6h, 24h $\pm$ 10min after injection, the injection site irritation score was observed and recorded before leaving the hospital. Local characteristics of the injection site should be inquired or visited during the follow-up period.
- 20) When subjects withdraw from the study, they should be checked as far as possible according to the safety evaluation on the second day after administration to complete the withdrawal visit.
- 21) If the analgesic reaction does not disappear, continue to observe in the phase I experimental ward until the analgesic reaction disappears before leaving the hospital.
- 22) Follow-up was conducted on days 7 $\pm$ 2 and 21 $\pm$ 3 after administration, and new local skin irritant reactions, adverse events (including SAE) at the injection site from discharge to day 21, and drug combinations were asked.

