- 22) Telephone follow-up was conducted on days  $7 \pm 2$  and  $21 \pm 3$  after administration, and new local skin irritant reactions, adverse events (including SAE) at the injection site occurred from discharge to day 21, and the situation of combined medication were asked.

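### The last follow-up contact may be made from day 18, so it cannot always cover the 21-day adverse event window that the protocol sets (minor)

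*Protocol*

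**What the plan says.** **Collection period.** The section on adverse event collection time reads: "Adverse events were recorded from the time subjects received the investigational drug to 21 days after the drug was administered".

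**Last contact, dose-finding part (Table 9, note 22).** "Follow-up was conducted on days 7 $\pm$ 2 and 21 $\pm$ 3 after administration". The contact has to cover the time "from discharge to day 21, and drug combinations were asked".

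**Last contact, dose-escalation part (Table 10, note 22).** "Telephone follow-up was conducted on days $7 \pm 2$ and $21 \pm 3$ after administration". Its scope is "new local skin irritant reactions, adverse events (including SAE) at the injection site occurred from discharge to day 21".

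**Later contacts.** None is listed. The Trial period section and the two flow charts end with the day 21 follow-up.

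**Analysis section (Statistical analysis method, Adverse events).** "The evaluation period shall be from the time of receiving the investigational drug to 21 days after the end of study or administration".

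**Use of the assessment (text under Table 1).** "Safety assessments were conducted on days 7 and 21 after dosing, and the next cohort/batch trial was determined based on the results".

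**The concern.** The protocol fixes an end to adverse event recording and names one contact that can close the period, but lets that contact happen before the period ends. The conflict lies within note 22 itself. A contact on day 18, 19 or 20 meets the timing tolerance, yet it cannot ask about events up to day 21, because those days have not yet happened.

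Safety and tolerability is the first of the main objectives. In the dose-escalation part, scheduled irritation scoring stops at 72 h and scheduled laboratory tests stop on day 4. After discharge, the two telephone contacts are therefore the only scheduled source of new adverse event information. If the second one is early, the length of prompted follow-up differs between subjects, while incidence is reported as if it covered one common 21-day period.

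A smaller point of wording adds to this. The analysis section gives the evaluation period two possible anchors, end of study or administration, whereas the collection section uses administration only.

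**Working it through.** No sample size or error rate is involved, so the check is day arithmetic plus a reading of the other reporting routes.

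**Inputs**
- End of collection: day 21 after administration (Adverse event collection time).
- Last contact: day 21, tolerance 3 days either way (note 22 of Tables 9 and 10).
- Later contacts: none scheduled.
- Subjects dosed: 3 in the dose-finding part and 41 in the dose-escalation part, 44 in all (Study design).

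**Permitted contact days.** Earliest 21 − 3 = 18; latest 21 + 3 = 24. That is 24 − 18 + 1 = 7 permitted days.

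**Uncovered tail.** For a contact on day c, the tail is max(0, 21 − c).

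| Contact day | Days without scheduled questioning | Share of 21 days |
|---|---|---|
| 18 | 3 | 3/21 = 14.3% |
| 19 | 2 | 2/21 = 9.5% |
| 20 | 1 | 1/21 = 4.8% |
| 21 to 24 | 0 | 0% |

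The notes count days after administration, and the table does the same. If day 21 were instead a study day with dosing on day 1, as in the flow-chart columns, the longest tail would be 4 days: study day 18 is 17 days after dosing, and 21 − 17 = 4.

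**How many subjects.** The protocol does not say how contacts fall within the tolerance. The number with an incomplete window can be anything from 0 to 44 (0 to 100%).

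**Do other routes close the gap?**
- *Record and report of serious adverse events/pregnancy:* subjects are to report serious events up to 21 days. This covers serious events, unprompted, and not others.
- *Methods for detecting adverse events:* unsolicited information is accepted, but detection is tied to follow-ups and visits.
- *Observation, recording and reporting of adverse events:* every event after dosing is to be documented. This is a duty to record and creates no further contact.
- *Follow-up of events present at study termination:* this applies to events already known, not to new ones.

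The remaining gap is therefore a new, non-serious event that starts in the last 1 to 3 days, in a subject contacted early, and that the subject does not volunteer.

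**After the change.** With contacts allowed only on days 21 to 24, the tail is 0 for everyone, and the window has 24 − 21 + 1 = 4 permitted days.

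**The case against.** A symmetric tolerance around a final contact is common practice, and note 22 does state the coverage it wants. On that view the protocol does not leave out days 19 to 21; it pairs a clear coverage rule with a loose tolerance. This is fair, and it is why the point is minor. The two conditions still cannot both be met before day 21, and nothing says which one yields.

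Several stronger readings are tempting, but the documents do not support them:

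- **That the last days are never asked about.** This is true only of scheduled questioning after an early contact. Contacts on days 21 to 24 leave no gap, and serious events can still be self-reported.
- **That about 43% of subjects are affected.** Contacts spread evenly over the seven days would give 3/7 = 43%, about 19 of 44, with a mean loss of (3 + 2 + 1)/7 = 0.86 day. The protocol gives no basis for an even spread, and the stated target is day 21.
- **That late reactions to the oil depot would be missed.** The section on possible adverse events lists ulceration, scab and fibrosis from preclinical work, but gives no onset times. Reactions that began earlier would be asked about at the day 7 contact and at the last one, and then followed up.
- **That escalation decisions would change.** The safety analysis is descriptive, and the termination criteria need related events of sufficient grade in at least 1/2 or 1/3 of a cohort, or a related serious event. A late, unprompted event could tip such a count in principle, but no event rate is given to show that it would.
- **That the analysis section demands 21 days of follow-up after the end of study.** That reading is possible but less natural, since the other safety sections anchor on dosing. It is an ambiguity of wording.

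**Conclusion.** The inconsistency is real and minor. The protocol's 21-day adverse event period is not guaranteed by its own contact schedule, in either part of the trial, because the last contact may be made on day 18 and nothing follows it. The loss is at most 3 of 21 days per subject (14%) and is zero for contacts on day 21 or later. It mainly affects new-onset, non-serious events. The share of subjects affected cannot be known from the protocol, and the effect on reported incidence is likely small, though where it occurs it can only lower the count. The figures assume that days are counted from administration, as note 22 says.

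**What to change.** 1. In note 22 of Tables 9 and 10, make the last contact window one-sided: day 21, +3 days, counted from administration. Alternatively, keep the present tolerance and require a repeat contact on or after day 21 whenever the contact was made earlier.
2. In the adverse events part of the statistical analysis method, tie the evaluation period to administration only, so that it matches the collection section.

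**Cost.** Two footnotes and one sentence change. The one-sided window adds no visits. Its price is 4 permitted contact days instead of 7. The latest permitted day, day 24, stays the same. The earliest moves from day 18 to day 21, which could delay by up to 3 days any step that waits for that contact. The alternative keeps the wider window at the price of one extra call for each subject contacted early.

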### Criteria for judging the severity of adverse events

The severity of adverse events was determined according to CTCAE (V5.0) criteria. In case of unlisted adverse events, the following table can be used for reference:

**Table 5: Criteria for determining adverse events**

| Adverse event classification | Severity description                                                                                                                                                                                                                                                                                                                     |
|------------------------------|------------------------------------------------------------------------------------------------------------------------------------------------------------------------------------------------------------------------------------------------------------------------------------------------------------------------------------------|
| Grade I:                     | Mild, with no or mild clinical symptoms; Only clinical or laboratory tests are abnormal; No treatment is required.                                                                                                                                                                                                                       |
| Grade II:                    | Moderate, requiring minimal, local, or non-invasive treatment; Age-appropriate Activities of Daily Living (ADL) using tools are limited, which means cooking, shopping, making phone calls, etc.                                                                                                                                         |
| Grade III:                   | Serious or medically serious condition but not life-threatening for the time being; Resulting in hospitalization or prolonged hospitalization; Cause disability; Self care ADL is limited. Daily self-care refers to taking a bath, dressing, undressing, eating, going to the bathroom, taking medicine, etc., and being not bedridden. |
| Grade IV:                    | Life-threatening and in need of urgent medical attention.                                                                                                                                                                                                                                                                                |
| Grade V:                     | Death due to adverse events.                                                                                                                                                                                                                                                                                                             |

### Evaluation of association between adverse events and experimental drugs

According to the judgment criteria of causality between drugs and adverse events, the correlation between adverse events and the application of tested drugs was divided into five levels: positively relevant, probably relevant, possibly relevant, possibly irrelevant and definitely irrelevant. The positive, probable and probable adverse drug reactions were classified as adverse drug reactions. Taking the total number of adr cases as the molecule, all selected cases for evaluation of adverse reactions as the denominator, the incidence of adverse reactions was calculated.

- ① **Positively relevant:** Fits the known pattern of reactions to the drug in question, consistent with a reasonable post-medication chronology, adverse events reduced or disappeared after dosage reduction or withdrawal. This adverse event occurred again after repeated administration..
- ② **Probably relevant:** Fits the known pattern of reactions to the drug in question, consistent with a reasonable post-medication chronology, adverse events reduced or disappeared after dosage reduction or withdrawal. However, the subject's clinical status or other reasons may also produce this event.
- ③ **Possibly relevant:** Fits the known pattern of reactions to the drug in question, consistent with a reasonable post-medication chronology, the adverse event was reduced or not significant after dosing reduction or withdrawal, but the clinical status of the subject or other reasons could explain the event.
- ④ **Possibly irrelevant:** Not very consistent with the known type of reaction of the drug in question, not very consistent with a reasonable time sequence after administration. The subject's clinical status or other causes may also have contributed to this event.
- ⑤ **Definitely irrelevant:** Does not conform to the known reaction type of the drug in question, does not conform to a reasonable time sequence after administration, the response can also be explained by the subject's clinical status or other causes, and the event abates or disappears when clinical symptoms or other causes are excluded.

**Table 6 Criteria for judging causality of adverse events**

|                                                    | Positively relevant | Probably relevant | Possibly relevant | Possibly irrelevant | Definitely irrelevant |
|----------------------------------------------------|---------------------|-------------------|-------------------|---------------------|-----------------------|
| Have a reasonable time sequence with the test drug | +                   | +                 | +                 | —                   | —                     |

|                                                            |   |   |   |   |   |
|------------------------------------------------------------|---|---|---|---|---|
| Known types of adverse drug reactions                      | + | + | + | — | — |
| The reaction relieved or disappeared after drug withdrawal | + | + | ± | ± | — |
| Adverse reactions returned after repeated administration   | + | ? | ? | ? | — |
| It can't be explained by the subject's disease             | + | + | ± | ± | — |

Note: (1)“+”certainty; “—”negative; “±”It is difficult to say or deny; “?”unclear situation; (2)Definitely related, may be related, can not determine the adverse reaction caused by drugs.

#### **Treatment, follow-up, and duration of cases with adverse events**

The investigator shall follow up the subject closely after the initial adverse event report, take appropriate treatment measures if necessary, and provide relevant information to the sponsor. All adverse events during the study, which should be managed according to the clinical trial center SOP, should be followed up to baseline or stable or lost to follow-up.

#### **Determination and treatment of abnormal laboratory test indicators**

Abnormalities in laboratory values must first be compared with baseline by the investigator to determine whether they are clinically significant; Adverse events were reported if laboratory abnormalities were judged to be clinically significant and varied from baseline. Non-clinically significant laboratory numerical abnormalities are not reported as adverse events. All abnormal laboratory test values/vital signs should be accurately recorded on the relevant case report form or eCRF.

